## 5 STUDY PROCEDURES

Sites will register patients into the SPUtNik study by sending a signed registration form by Fax or email attachment to SCTU (numbers listed at front of protocol). Sites will be given a block of SPUtNik codes. Sites will allocate trial ID codes consecutively following consent. On registration SCTU staff will check eligibility and confirm the patient study number by email. Both registration and the DCE-CT scan must not take place before informed consent is signed, however registration with SCTU may take place before or after the DCE-CT scan, as some clinics may schedule the DCE-CT scan outside of office hours.

### 5.1 BASELINE & EVALUATIVE PROCEDURES (Visit 1, Day 0)

#### **Pre-Scan Tasks.**

These tasks must be completed before study DCE –CT scans are performed:

- Informed consent checked or taken
- SPUtNik trial code written on front of IPCARD-SPN Questionnaire and collection of completed questionnaires (for patients who have consented to sub study)
- Patients wishing to complete the IPCARD-SPN Questionnaire at home will be given a Free-Post return envelope to return the questionnaire

#### **Scans:**

- F-DG-PET/CT performed in line with procedure described in Appendix 2
- DCE-CT performed in line with procedure described in Appendix 3

If both scans are performed on the same day F-DG-PET/CT should be performed first with no waiting time required between scans. If scans are performed on separate days either scan can be performed first provided that patient consent and registration takes place before the DCE-CT scan (e.g. in the case of a delay in F-DG-PET/CT).

F-DG-PET/CT and DCE- CT scans will ideally be performed within 14 days – however, an absolute maximum of 21 days is allowed between scans should sites have difficulty with scheduling.

### 5.2 PATIENT MANAGEMENT FOLLOWING PET-CT AND DCE-CT

Following the PET-CT and DCE-CT investigations, management of the SPN should be directed by the local/specialist lung MDT.

In many cases nodule biopsy or excision biopsy may be undertaken. Those cases shown to be due to lung cancer (or other malignancy) will be managed according to local protocols. Follow up/outcome data will be collected by CRF.

In some cases it is recognised that nodule surveillance is appropriate (with or without prior biopsy). In these cases it is recommended that follow up is performed at

- 3 months
- 9 months
- 24 months

as per Fleischner Society Guidelines (Radiology 2005;237:395) for management of indeterminate nodules >8mm. (Deviation from these time points based on clinical need is at the discretion of the MDT)

At each visit the following should be performed:

- Chest CT (low dose, thin section, unenhanced) unless MDT feels it is inappropriate
- Recording of any biopsy samples taken

- Recording of health resource use information

At 2 years

- Health resource data will be collected from patient records
- The end of study CRF will be completed in the InForm Database
- The PI will sign off the patients electronic CRF record and the database will be locked for that patient

### **5.3 PROCEDURE TO FOLLOW WHEN NODULE IS REDUCED OR NOT VISIBLE ON DCE-CT SCAN**

Occasionally a nodule which was eligible (8-30mm) on lung window on qualifying CT scan has a reduced size or is not visible on mediastinal window some weeks later when the DCE-CT scan is to be performed. The reason for this may be that the nodule has resolved completely or reduced in size, due to it having an infection or inflammatory component. In this case the procedures below should be followed:

- If nodule is not visible on DCE-CT locating scan – Contrast should not be administered and procedure should be aborted
- If nodule has reduced in size but is visible on DCE-CT locating scan with a minimum diameter of 8mm - Contrast should be administered and DCE-CT procedure followed
- If the nodule is between less than 8mm on the locating scan the decision to continue with contrast administration is to be made by the local radiologist who will assess if the nodule can be reliably reported.

Follow up and outcome data should be collected on all patients.

### **5.4 ACCESS TO OUTCOME DATA**

If patients are lost to follow up within 2 years (e.g. relocation to another health authority) outcome data will be obtained via the Health and Social Care Information Centre. Consent for this will be taken during initial consenting process.

### **5.5 WITHDRAWAL CRITERIA**

A patient can withdraw consent at any time. They will not be asked to give a reason for withdrawal of consent.

- If a patient withdraws from undergoing PET-CT or DCE-CT or both scans, but does not specifically withdraw consent to collect data from hospital notes , collection of relevant data from their hospital notes and GP contact should continue as per protocol.
- If consent is completely withdrawn, results may only be recorded on CRFs for procedures performed prior to the withdrawal of consent.

## **6. SAFETY OVERSIGHT**

Safety oversight for this study is centered on the effects of injection of the contrast material and increased radiation from the DCE-CT scan that participants will undergo in addition to current practice. To be applicable to patients identified within a future CT screening programme, the radiation dose associated with the DCE-CT is kept as low as reasonably applicable and comparable to many other imaging tests commonly used in clinical practice. The contrast agent required for DCE-CT is used extensively in clinical practice.

Adverse events will be recorded for 30 days following the DCE-CT study scan. It is envisaged that any adverse events due to radiation will be apparent within 7 days. Patients will remain in the scanner centre for at least 20 minutes following contrast injection to check and treat any immediate adverse effects. They will be given a card with the study details, DCE-CT and contrast used and local research contact details. Patients will be asked to show the card to any person that they seek medical advice from in the next 30 days and also to contact the research team if they feel unwell over the next 30 days.

All trial information will be kept for 15 years.

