| 4-6 hr Fasting Glucose                     |                                  | X                                           |                                  |                                  |                      |                |
| Resource Assessment                                    |                                  |                                             |                                  |                                  |                      | X              |
| Sub-Study IPCARD Questionnaire                         |                                  | X                                           |                                  |                                  | X                    |                |
|  F  FDG-PET  |                                  | X                                           |                                  |                                  |                      |                |
| DCE-CT                                   |                                  | X                                           |                                  |                                  |                      |                |
| Chest CT                                 |                                  |                                             | X                                | X                                |                      | X  |
| Concomitant Medications                                | X                                |                                             |                                  |                                  |                      |                |
| Adverse Events                             |                                  | X                                           |                                  |                                  |                      |                |

 Method in accordance with standard hospital procedure for FFDG-PET.

 Chest CT scans will be performed only on patients without definitive pathological findings

 FFDG-PET and DCE-CT scans will be performed on the same day. If not possible, they should ideally be done within 14 days but no longer than 21 days.

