 Adverse events will be recorded from DCE scan date for up to 30 days after DCE-CT scan. No effects of contrast medium are expected after 7 days

 Copies of Scan reports will be anonymised and sent to SCTU

 Baseline visit may consist of a number of actual visits, depending if PET and DCE-CT scans are performed on the same scanner and if consent is taken at scan appointment or during a separate appointment

 visits 2-3 will only take place for patients in whom the SPN remains undiagnosed, for patients where the scans are suggestive of lung cancer visits 2 and 3 may represent biopsy or treatment visits.

 this will only take place for patients in whom the SPN remains undiagnosed.

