## 6.3 REPORTING PROCEDURES

All adverse events for 30 days following the DCE-CT study scan should be reported on the SPUtNIK database.

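### All adverse events are required to day 30 after DCE-CT, but no enquiry is scheduled after the scan day, so delayed, mainly mild events are likely to be under-counted

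*Protocol*

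**What the plan says.** Three places set the window. Protocol section 6 states: "Adverse events will be recorded for 30 days following the DCE-CT study scan". Section 6.3 adds: "All adverse events for 30 days following the DCE-CT study scan should be reported on the SPUtNIK database". Footnote 4 of the Schedule of Observations and Procedures has: "Adverse events will be recorded from DCE scan date for up to 30 days after DCE-CT scan".

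The scope is wide. Section 6.1 defines an adverse event regardless of cause, section 6.3.2 covers non-serious events, and section 6.3.1 counts a pre-existing condition that worsens by at least one CTCAE grade within the 30 days.

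On method, the adverse-event row of the schedule carries a single mark, under Visit 1 (day 0). Section 6 describes one period of direct observation: "Patients will remain in the scanner centre for at least 20 minutes following contrast injection". For the rest of the window it relies on the patient. "Patients will be asked to show the card to any person that they seek medical advice from in the next 30 days", and they are asked "also to contact the research team if they feel unwell over the next 30 days". Under section 6.3.3, a site sends a serious adverse event form within 24 hours of becoming aware of the event.

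Visit 2 is set at 3 months or local practice and has no adverse-event mark. Footnote 7 limits it: "visits 2-3 will only take place for patients in whom the SPN remains undiagnosed".

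**The concern.** The count asked for is a complete 30-day, all-cause count. The method supplied for days 1 to 30 is spontaneous notification. Patients asked only to report feeling unwell are an unreliable source for a mild delayed reaction or a one-grade worsening of an existing condition. A site that follows the protocol exactly can finish day 30 without having asked anyone anything.

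If the resulting figures are presented as a 30-day adverse-event rate, they will look more complete than they are. Section 6 centres safety oversight on the contrast and radiation that DCE-CT adds to current practice, with a future screening population in mind, so how these events are described has some importance even though they are not a trial outcome.

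**Working it through.** **1. Required against provided.**

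| Item | Required | Provided |
|---|---|---|
| Period | Scan date to day 30 (section 6, section 6.3, footnote 4) | Mark at day 0 only (schedule) |
| Events | All, serious and non-serious (sections 6.1, 6.3, 6.3.2) | Observation of at least 20 minutes, then card, patient contact, site awareness (sections 6, 6.3.3) |
| Patients | Everyone scanned | Same passive routes for everyone |

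No adverse-event enquiry is fixed between day 1 and day 30 for any of the 375. Some patients will attend inside the window anyway, for example for PET/CT when DCE-CT is done first (section 5.1 allows up to 21 days between scans), or for a biopsy. No adverse-event question is tied to those attendances.

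**2. Does anything later close the gap?**

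- Visit 2 at 3 months is about day 91 (3 × 30.4), some 91 − 30 = 61 days after the window ends. Local practice may move it, but it carries no adverse-event mark.
- The follow-up list in section 5.2 covers chest CT, biopsy samples and resource use.
- The 24-month notes review in section 8.4 covers management and cost items, including inpatient stays. Section 7 has resource data collected for all patients for 2 years from the DCE-CT scan. An admission in days 0 to 30 should therefore be on file, though not identified as an adverse event. A mild event without an admission would not be.
- Section 6.3.4 asks the investigator to check resolution dates for events already recorded, which does not find new ones.

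**3. Is the gap larger in one group?** The plan's own split reproduces: 375 × 0.685 = 256.9, so 257 malignant, and 375 − 257 = 118 benign (section 9.1). The split does not bear on capture. Neither group has a fixed adverse-event enquiry inside the window.

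**4. Size.** The documents state no delayed-event rate and no capture rate, so the loss cannot be computed. The table is an illustration on assumed values: patients recorded = 375 × true rate × capture.

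| Assumed true rate | 100% capture | 75% | 50% | 25% |
|---|---|---|---|---|
| 1% | 3.8 | 2.8 | 1.9 | 0.9 |
| 3% | 11.3 | 8.4 | 5.6 | 2.8 |
| 5% | 18.8 | 14.1 | 9.4 | 4.7 |

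If no delayed event were recorded in 375 patients, the one-sided 95% upper limit with full capture is 1 − 0.05^(1/375) = 0.80%. Dividing by the assumed capture gives about 1.1% at 75%, 1.6% at 50% and 3.2% at 25%. With an assumed true rate of 1%, the chance of recording none is 0.99^375 = 2.3% with full capture and 0.995^375 = 15% at half capture.

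**The case against.** The strongest reply is that the protocol does not contradict itself. The Visit 1 mark carries footnote 4, which extends recording to day 30, and section 6 states how events in that period are to reach the team. A fixed window with spontaneous reporting is a coherent choice. That is fair: the weakness is that a passive method is paired with a demand for all events, not that two passages conflict.

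The serious end is also better covered than the schedule alone suggests. Sites report serious events once aware of them, and inpatient stays are extracted from the scan date onward. What can be lost is mainly mild and non-serious. The protocol further expects no contrast effects after 7 days (footnote 4) and radiation effects to be apparent within 7 days (section 6), so much of what is missed late in the window may be background illness. That limits the consequence, but days 1 to 7 still lie beyond the scan-day observation.

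Adverse events are neither a primary nor a secondary outcome (section 3.1), and section 9.1 plans no analysis of their rate. This stands, and it sets the severity.

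A reader might also infer that the loss is worst among the roughly 257 patients with malignant nodules, because most would have no surveillance visit, and that missingness therefore depends on diagnosis. The documents do not support this. Surveillance visits bring no adverse-event enquiry inside the window to anyone, and footnote 7 says that Visits 2 and 3 may be biopsy or treatment visits when scans suggest cancer. Those patients may have more clinical contact, so any difference could run either way.

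**Conclusion.** The point holds and is minor. The protocol requires all adverse events to day 30, schedules its only assessment on the scan day, and leaves the rest of the window to passive reporting in every patient. Under-counting of delayed, mainly mild events is likely; this is an inference from the method, and the documents do not allow its size to be computed. The figures above rest on assumed event and capture rates and show only how the count would respond.

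Diagnostic accuracy results, sample size and planned analyses are unaffected. A reader might go further and say that a safety conclusion about adding DCE-CT to NHS practice rests on this count, or that the result is little more than a 20-minute rate. The text supports neither: no stated conclusion depends on the count, and the card, patient contact, site reporting of serious events and extraction of inpatient stays all add to it.

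**What to change.** - Add a Day 30 adverse-event entry to the schedule for every patient who had DCE-CT. Existing research staff would complete it from hospital records, with a short call where practical, since records alone may miss mild events.
- Add a yes/no field to the 24-month extraction form for any admission, attendance or death in days 0 to 30, using the resource data already collected from the scan date. The field would prompt a check against the adverse-event record. The exemptions from serious-event reporting in section 6.3.3 would stay as they are.
- Report scan-day events separately from those on days 1 to 30.
- If no active check is added, describe the day 1 to 30 events as spontaneously reported.

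The cost is one CRF entry, one form field and a few minutes of existing staff time per patient: 375 × 10 minutes (assumed) = 62.5 hours in total. No extra visit or procedure is needed.

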## 6.1 DEFINITIONS

**Adverse Event (AE):** any untoward medical occurrence in a patient or clinical trial subject which does not necessarily have a causal relationship with trial treatment or participation.

**Serious Adverse Event (SAE) :** any untoward medical occurrence or effect that at any dose:

- **Results in death**
- **Is life-threatening** – *refers to an event in which the patient was at risk of death at the time of the event; it does not refer to an event which hypothetically might have caused death if it were more severe*
- **Requires hospitalisation, or prolongation of existing inpatients' hospitalisation**
- **Results in persistent or significant disability or incapacity**
- **Is a congenital anomaly or birth defect**

Medical judgement should be exercised in deciding whether an AE is serious in other situations. Important AEs that are not immediately life-threatening or do not result in death or hospitalisation but may jeopardise the patient or may require intervention to prevent one of the other outcomes listed in the definition above, should also be considered serious.

## 6.2 CAUSALITY

The assignment of the causality to trial treatment of any serious event should be made by the investigator responsible for the care of the patient using the definitions in the table below.

If any doubt about the causality exists the local investigator should inform the SCTU who will notify the Chief Investigator. Other clinicians may be asked for advice in these cases.

In the case of discrepant views on causality between the investigator and others, all parties will discuss the case. In the event that no agreement is made, the Ethics Committee will be informed of both points of view.

| Relationship | Description                                     |
|--------------|-------------------------------------------------|
| Unrelated    | There is no evidence of any causal relationship |

|                   |                                                                                                                                                                                                                                                                                        |
|-------------------|----------------------------------------------------------------------------------------------------------------------------------------------------------------------------------------------------------------------------------------------------------------------------------------|
| Unlikely   | There is little evidence to suggest there is a causal relationship (e.g. the event did not occur within a reasonable time after the test scan). There is another reasonable explanation for the event (e.g. the subject's clinical condition, other concomitant treatment).            |
| Possible   | There is some evidence to suggest a causal relationship (e.g. because the event occurs within a reasonable time after the test scan). However, the influence of other factors may have contributed to the event (e.g. the subject's clinical condition, other concomitant treatments). |
| Probable   | There is evidence to suggest a causal relationship and the influence of other factors is unlikely.                                                                                                                                                                                     |
| Definitely | There is clear evidence to suggest a causal relationship and other possible contributing factors can be ruled out.                                                                                                                                                                     |

## 6.3 REPORTING PROCEDURES

All adverse events for 30 days following the DCE-CT study scan should be reported on the SPUtNIK database.

### 6.3.1 Pre-existing Conditions

A pre-existing condition should not be reported as an AE unless the condition worsens by at least one CTCAE (version 4.0) grade up to 30 days following the DCE-CT scan.

### 6.3.2 Non serious AEs

All adverse events should be recorded in the adverse event section of the online SPUtNIK InForm database and should be followed up until resolution.

### 6.3.3 Serious AEs

If an AE is considered serious (see definition in 6.1) In addition to recording the event in the database a paper SAE/SUSAR form should be completed and faxed to SCTU within 24 hours of site becoming aware. The SAE form can be completed by any member of the research team at site, but causality must be made by the Principal Investigator or delegated to the investigator responsible for the care of the patient. If the causality cannot be assigned within 24 hours the partially completed SAE form should be faxed to SCTU and refaxed when the PI or investigator responsible for the care of the patient is available to sign it.

The SAE/SUSAR form asks for nature of event, date of onset, severity, corrective therapies given, outcome and causality (i.e. unrelated, unlikely, possible, probably, definitely). The responsible investigator should assign the causality and expectedness of the event. Additional information should be provided as soon as possible if the event/reaction has not resolved at the time of reporting.

Diagnosis or progression of lung cancer or death, due to lung cancer and hospitalisations for elective treatment of a pre-existing condition do not need reporting as SAEs.

## **SAE/SUSAR REPORTING CONTACT DETAILS**

*Please email or fax a copy of the SAE/SUSAR form to  
SCTU within 24 hours of becoming aware of the event*

**[contact] or Email: [[contact]](mailto:[contact])**

**FAO: Quality and Regulatory Team**

***For further assistance:***

***[contact] (Mon to Fri 09.00 – 17.00)***

The SCTU will notify the necessary REC of all SUSARs occurring during the trial according to the following timelines; fatal and life-threatening within 7 days of notification and non-life threatening within 15 days. All investigators will be informed of all SUSARs occurring throughout the trial.

Local investigators should report any SUSARs and /or SAEs as required by their Local Research Ethics Committee and/or Research & Development Office.

### **6.3.4 Follow Up for AE/SAEs**

All adverse events should be followed by the investigator until resolved, the patient is lost to follow-up, or the adverse event is otherwise explained. When the investigator fills in an end of study form on the SPUtNIK online database they should check that all resolution dates have been recorded for AEs and SAEs before signing the case report form as complete in the database.

